### Plans to promote participant retention and complete follow-up {18b}

Longitudinal follow-up data are important in clinical trials [57, 58]. Generally, issues with the collection of follow-up data can be summed up in the following categories: (1) unable to contact, (2) unable to complete, (3) refusing, and (4) unable to locate [57]. The loss of follow-up data due to subject attrition is a frequent cause of loss of statistical power or increased risk of bias, which minimizes the generalizability and validity of a clinical trial [57, 59]. Consequently, a robust plan for obtaining follow-up data is important. At the initial assessment, we focus on building rapport and positive interactions between participants and clinicians. This fosters participants’ commitment to both the project and staff [57]. We will build rapport through genuine interest in participants’ issues, history, and potential questions regarding project participation. Prospective participants are informed about the project’s goals, the importance of completing participation, and the personal benefits of participation. These strategies may raise the level of adherence throughout our study [59]. Obtaining accurate personal and demographic data is important in locating and contacting participants during the participation period. Furthermore, at the initial assessment, we will also schedule approximate dates for gathering follow-up data. Having scheduled appointments should increase the likelihood that participants will attend both follow-up sessions. Likewise, after participants have been assigned to a treatment group, the therapist in each group will send written reminders the day before each scheduled therapy session. A strong and continuous focus on overcoming these barriers should maximize the number of participants that complete the follow-up assessments.

### Data management {19}

Study data is collected by the research staff and managed using REDCap electronic data capture tools hosted at the Capital Region Mental Health Services. PSG data will be electronically stored on a secure server provided by the Capital Region Mental Health Services, Denmark.

### Confidentiality {27}

The project will comply with the data protection regulation and data protection act (Databeskyttelseslov- og forordning). The project has been approved by the Danish Data Protection Agency under the common Capital Region Mental Health Services’ umbrella application. All data on a secured data-drive (REDCap). REDCap is a secure, web-based software platform designed to support data capture for research studies [60]. Data extracted for analyses will be handled as confidential data and pseudo-anonymized using project letters and ID numbers, which will be kept at closed, secured, and monitored data-drives. PSG data will likewise be kept in pseudo-anonymized form in a secured data folder. Only anonymized data will be published.

The data will be stored in REDCap until 31 December 2039. Subsequently, the data will be archived in fully anonymized form.

### Plans for collection, laboratory evaluation and storage of biological specimens for genetic or molecular analysis in this trial/future use {33}

Not applicable, no biological specimens obtained.

## Statistical methods

### Statistical methods for primary and secondary outcomes {20a}

Repeated measure ANOVA will be used to identify group differences for ISI and the secondary outcome measures, between baseline, 12 and 24 weeks, and post hoc *t*-tests will be performed when relevant. Analyses at both timepoints are performed in order to identify an immediate and a lasting effect. Due to the novelty of the intervention, particularly in this patient group, and the rather unclear causal relationship between sleep and psychosis, we consider the secondary outcome analyses as exploratory and therefore correction for multiple testing will not be performed.

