### Outcomes {12}

The primary outcome is improvement of the individual ISI score after 12 weeks. Secondary outcome measures are ISI score after 24 weeks and changes in PANSS (both total and subscale scores) [44], Global Assessment of Functioning (GAF) [45], WHO Well-Being Index (WHO-5) [46], Functioning Assessment Short Test (FAST) [47], Personal and Social Performance Scale (PSP) [48], the Process of Recovery Questionnaire (QPR) [49], the Treatment Expectation Questionnaire (TEX-Q) [50] and PSG. All outcomes are measured at baseline, after 12 weeks, and at 24 weeks, except for PSG, which is only measured at baseline and after 12 weeks.

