### Sample size {14}

To reach a power of 80% (*α* = 0.05, *β* = 0.2) for detecting a between-groups effect of CBT-I on ISI of 4, follow-up data on 24 patients in each group is needed. Since an attrition rate of around 25% is expected, the aim will be to include a total of 60 patients. For the power calculation, means and standard deviations from a previous study were used [20]. However, the between-groups effect is expected to be less since we are using two active interventions.

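### The ISI analysis covers three visits and does not name the week-12 contrast as the test that decides the primary hypothesis

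*Protocol article*

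**What the plan says.** The section Outcomes {12} fixes the endpoint and its time: "The primary outcome is improvement of the individual ISI score after 12 weeks". The later visit has a lower rank: "Secondary outcome measures are ISI score after 24 weeks and changes in PANSS", followed by the other scales and polysomnography.

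The section Statistical methods for primary and secondary outcomes {20a} gives one method for all of these: "Repeated measure ANOVA will be used to identify group differences for ISI and the secondary outcome measures, between baseline, 12 and 24 weeks". It continues with "post hoc *t*-tests will be performed when relevant" and then "Analyses at both timepoints are performed in order to identify an immediate and a lasting effect". On multiplicity it says "we consider the secondary outcome analyses as exploratory and therefore correction for multiple testing will not be performed".

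Sample size {14} rests on a plain two-group difference: "for detecting a between-groups effect of CBT-I on ISI of 4, follow-up data on 24 patients in each group is needed", at 80% power and alpha 0.05.

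**The concern.** The outcomes section singles out week 12, while the analysis section treats baseline, week 12 and week 24 together. It does not say which ANOVA term answers the primary hypothesis, what triggers the follow-up t-tests, or whether those tests use raw scores or change. The sentence on both time points puts weeks 12 and 24 on an equal footing, although one is primary and the other secondary.

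Two things are at stake. First, a significant ISI result could be reported as supporting the primary hypothesis when the signal comes only from week 24. Second, several routes to a primary claim stay open until the data are seen. This matters more because the trial is mostly unblinded and ISI is self-reported. The waiver of multiplicity correction is argued for the secondary outcomes only and does not cover alternative routes to the primary conclusion.

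**Working it through.** **Inputs from the article.** 24 patients per arm with follow-up data, a difference of 4 ISI points, alpha 0.05 (two-sided assumed), power 80%, three visits.

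**Inputs assumed.** The article states neither the SD nor the correlation between visits. I use equal variances and one common correlation ρ of 0.3, 0.5 or 0.7, with 0.8 as a further check.

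**The stated sample size.** Without an SD it can only be solved backwards. With the normal approximation, n = 2·SD²·(1.960 + 0.842)²/4². Setting n = 24 gives SD² = 24·16/(2·7.85) = 24.5, so SD = 4.95. The two-sample t-test gives SD = 4.84, which I use below. This is circular, so it does not verify the 24.

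**Group-by-time test over three visits.** Let δj be the between-arm difference at visit j. The noncentrality is λ = (n/2)·Σ(δj − mean δ)²/[SD²(1 − ρ)], on 2 and 92 degrees of freedom.

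- Effects (0, 0, 4), with nothing at week 12: mean 4/3, sum of squares 16/9 + 16/9 + 64/9 = 10.67. At ρ = 0.5, λ = 12·10.67/(23.44·0.5) = 10.9.
- Effects (0, 4, 0) and (0, 4, 4) have the same sum of squares, 10.67. The test therefore cannot tell an effect at week 12 only from an effect at week 24 only.
- Effects (0, 4, 2): mean 2, sum of squares 4 + 4 + 0 = 8. At ρ = 0.5, λ = 8.2.

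With no week-12 effect and 4 points at week 24, this test rejects in 69% (ρ = 0.3), 84% (0.5) and 97% (0.7) of trials. A week-12 ANCOVA rejects in about 5%.

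**Week-12 ANCOVA.** λ = (n/2)·4²/[SD²(1 − ρ²)] on 1 and 45 degrees of freedom. At ρ = 0.5, λ = 192/(23.44·0.75) = 10.9. The formula gives power of 84%, 90% and 97.5%. Simulation, which includes chance baseline imbalance, gives about 83%, 89% and 97%. The effect at week 24 does not enter.

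**Power for 4 points at week 12.** Ranges run over the assumed effects at week 24. The two-step columns are simulated and require a significant interaction followed by a significant week-12 t-test.

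| ρ | Interaction alone | Two-step, raw scores | Two-step, change scores | Change from baseline to week 12 only | Week-12 ANCOVA |
|---|---|---|---|---|---|
| 0.3 | 56–69% | 51–63% | within 50–63% | 66% | 83% |
| 0.5 | 71–84% | 62–72% | 70–76% | 80% | 89% |
| 0.7 | 91–97% | 75–79% | 91–94% | 95% | 97% |

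At ρ = 0.8 the interaction has 99.8% against 99.7% for ANCOVA (by formula) if the effect is sustained, and 98.4% against 99.7% if it halves by week 24.

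**Error rate of the two-step rule.** With no week-12 effect and 4 points at week 24, requiring the raw-score week-12 t-test as well brings rejection down to about 4–5%. A wrong primary claim therefore arises if the omnibus result is taken as the answer, not if a week-12 test must also succeed.

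**The case against.** The strongest reply is that week 12 is tested. The analysis section says that both time points are analysed, and one fair reading is a baseline-to-12 analysis and a separate baseline-to-24 analysis. In a two-visit ANOVA the group-by-time test equals a t-test on change, which matches the stated outcome. This stands against any claim that the plan fails to test its primary outcome. It does not supply a designation: the text still leaves open whether that comparison, the three-visit interaction or a conditional t-test decides.

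A reader might also infer that the analysis falls short of 80% power. The article does not support that as a general statement. It nowhere says that success requires both the omnibus test and a t-test, and the shortfall depends on an unstated correlation and on whether change or raw scores are tested. At ρ = 0.5 with a sustained effect the interaction alone has 84%. The group main effect would do much worse, because it averages in the baseline visit, but the wording points to change across visits, so it is not the natural reading.

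Finally, naming the tested term is often left to an analysis plan, and one may exist. That would excuse silence. Here the protocol states a method that does not line up with its own ranking of the two visits, so the protocol text needs correcting in any case. Preferring ANCOVA to change scores is partly a matter of efficiency; the need to name one week-12 test is not.

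**Conclusion.** The concern holds in this form: the primary hypothesis is tied to week 12 in the outcomes section, but the analysis section does not make a week-12 contrast the deciding test. The three-visit interaction is not specific to week 12 and would reject in roughly 69% to 97% of trials on a 4-point effect at week 24 alone.

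The power cost is conditional. Compared with a baseline-adjusted week-12 contrast, the interaction loses about 14 to 27 points at ρ = 0.3 (83 − 69, 83 − 56) and 5 to 18 at ρ = 0.5 (89 − 84, 89 − 71). At ρ = 0.7 it loses between nothing and 6 points (97 − 97, 97 − 91). The two-step rule loses more if raw scores are tested. All of this rests on the back-solved SD, the assumed correlations, equal variances and complete data on 24 per arm. Neither a complete failure to test week 12 nor a loss of power under every assumption is supported.

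**What to change.** In the statistical methods section {20a}, name one primary test: the between-arm difference in ISI at week 12, adjusted for baseline ISI, two-sided at 0.05, reported with a 95% confidence interval. It can come from an ANCOVA or from the week-12 contrast of a mixed model that replaces the ANOVA. Make ISI at week 24 a secondary contrast. State that neither the omnibus ANOVA nor conditional post hoc t-tests decide the primary hypothesis. If an analysis plan exists, align it with this text.

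The cost is a protocol wording amendment. Baseline ISI is already collected, and no further patients or visits are needed. The article reports 5 patients included by January 2026, so the change can still be made well before the data are analysed.

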### Interim analyses {21b}

Not applicable, no interim analyses planned.

### Methods for additional analyses (e.g., subgroup analyses) {20b}

We also plan to analyze the data with a subgroup analysis of patients strictly fulfilling the TRRIP-criteria. 

### Methods in analysis to handle protocol non-adherence and any statistical methods to handle missing data {20c}

Included in the analysis population will be patients who have completed four therapy sessions. We will use the Last Observation Carried Forward (LOCF)-principle as an imputation method for handling missing data for intention-to-treat (ITT) analyses.

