### Trial design {8}

This is a 12-week non-blinded randomized controlled trial (RCT) with a superiority framework. Patients will be randomized 1:1 using a block randomization regimen with variable block sizes (2, 4, and 6), which is done to achieve equal sample size in different groups over time [30]. For a flowchart of the trial, see Fig. 1.

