### Intervention description {11a}

Included patients will be randomized 1:1 to CBT-I with a specific focus on sleep or regular CBT with a specific focus on patients’ psychopathology and related difficulties. The interventions are delivered by two different psychologists with similar experience in the field.

Patients randomized to the CBT-I arm will receive a manualized intervention, specifically adapted for individuals with severe mental illness and sleep disturbances. The intervention is delivered individually over 8–10 sessions at UCS, scheduled approximately once per week across a 12-week period. The duration of sessions varies according to the treatment phase:Session 1 (Initial assessment): 60–120 minSession 2 (Treatment initiation): 60–120 minSessions 3–8 (Titration and relapse prevention): 45–60 min each

The extended duration of the first two sessions is necessary to allow for comprehensive assessment, individualized treatment planning, and thorough patient education.

The treatment protocol follows a Danish CBT-I manual developed for the COSTS project, which follows the general structure of previous manuals [42]. The first session includes a comprehensive assessment of sleep problems, confirmation of inclusion criteria, and introduction to the sleep diary, which patients are instructed to complete daily throughout the intervention. The sleep diary is used both for baseline assessment (between the first and second session) and as an ongoing tool to guide individualized treatment adjustments.

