### Criteria for discontinuing or modifying allocated interventions {11b}

The psychotherapeutic intervention in both groups will be adjusted continuously for each trial participant given the individual nature. In the unlikely event that either intervention should result in a worsening of the psychotic symptoms, both the participant and the clinician providing the intervention can decide to discontinue the intervention, ideally in a way resembling shared decision-making.

Furthermore, 2 untimely cancelations or failures to appear in a row are considered non-compliance with the treatment, and the participant is excluded from the study.

Lastly, a change in a participant’s psychopathology which results in either substantial changes in antipsychotic medication or admittance lasting ≥ 7 days will result in exclusion from the study as per the exclusion criteria.

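### The only analysis population defined is patients with four completed sessions, a post-randomisation selection that cannot be the set for the intention-to-treat analyses named in the next sentence

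*Protocol article*

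**What the plan says.** The section on non-adherence and missing data {20c} consists of two sentences. The first sets the population: "Included in the analysis population will be patients who have completed four therapy sessions". The second reads: "We will use the Last Observation Carried Forward (LOCF)-principle as an imputation method for handling missing data for intention-to-treat (ITT) analyses". No all-randomised, modified intention-to-treat or per-protocol set is defined anywhere in the article. The section on statistical methods for the primary and secondary outcomes {20a} names the tests but no population.

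Four other places bear on the point:

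- **Design and timing.** Trial design {8} describes a "non-blinded randomized controlled trial (RCT) with a superiority framework". The participant timeline {13} puts randomisation at the baseline visit, ahead of the first session.
- **Length of therapy.** Intervention description {11a}: "The intervention is delivered individually over 8–10 sessions at UCS". Four sessions are therefore 40% to 50% of a course (4/10 to 4/8).
- **Stopping therapy.** Under {11b}, if psychotic symptoms worsen, "both the participant and the clinician providing the intervention can decide to discontinue the intervention".
- **Leaving the study.** Also under {11b}, two consecutive late cancellations or no-shows "are considered non-compliance with the treatment, and the participant is excluded from the study". A substantial antipsychotic change or an admission of at least 7 days "will result in exclusion from the study as per the exclusion criteria".

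**The concern.** Completing four sessions depends on what happens after allocation: tolerability, early response, worsening and attendance. A set defined that way is a completer or per-protocol set. An intention-to-treat set keeps every randomised patient, so the two sentences in {20c} cannot describe the same set.

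The choice matters in this trial for three reasons. Therapy is open and the primary outcome is self-reported. Session count can depend on outcome, because therapy may be stopped for worsening psychosis under {11b} and for worsening psychosis or sleep under the adverse-event section {22}. The content of therapy also differs between arms: only CBT-I includes sleep restriction, and the Discussion itself treats this as carrying some risk for psychosis. If the chance of reaching four sessions, or its relation to outcome, differs by arm, the completer contrast no longer estimates the effect of being assigned to CBT-I.

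Because no analysis is named as primary, the choice could also be made after open-label results have been seen.

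**Working it through.** **1. The text.** Take a randomised patient with three sessions and a complete 12-week ISI. Under the first sentence of {20c} the patient is out. Under the intention-to-treat label in the second, the patient is in. The article gives no rule for deciding between them. This step needs no arithmetic, and the finding rests on it.

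**2. The SD behind the plan's own figure.** The sample-size section {14} gives a 4-point difference, α = 0.05, 80% power and 24 per group, but no SD. Solving backwards with the normal approximation, two-sided:

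SD = 4 / [(1.960 + 0.842) × √(2/24)] = 4 / (2.802 × 0.2887) ≈ 4.95

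The exact t-test gives about 4.84 two-sided and about 5.5 one-sided. The article does not state sidedness. I use 4.84 as an assumption.

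**3. Illustrative bias with no true effect.** Assumptions: 30 per arm; in each arm the fraction f with the highest values of a score correlated ρ with 12-week ISI falls short of four sessions. The mean of those retained is then shifted by

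−ρ × SD × k(f), where k(f) = φ(z) / (1 − f), φ is the standard normal density and z is its (1 − f) quantile.

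- k(0.10) = 0.1755/0.90 = 0.195
- k(0.20) = 0.2800/0.80 = 0.350
- k(0.30) = 0.3477/0.70 = 0.497

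The bias is the difference between the arms' shifts. The type I error comes from simulation.

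| Scenario | Bias (ISI points) | Type I error |
|---|---|---|
| Equal loss, same mechanism in both arms | about 0 | about 5–6% |
| 30% v 10% loss, ρ = 0.3 in both | 0.3 × 4.84 × (0.497 − 0.195) = 0.44 | about 6% |
| 30% v 10% loss, ρ = 0.5 in both | 0.5 × 4.84 × 0.302 = 0.73 | about 8–9% |
| 20% loss in each arm, ρ = 0.5 in CBT-I only | 0.5 × 4.84 × 0.350 = 0.85, favouring CBT-I | about 9% |
| 20% loss in each arm, ρ = 0.5 in control only | 0.85, favouring control | about 9% |

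Simulated biases agree with the formula to within a few hundredths of a point. In the 30% v 10% rows the bias favours whichever arm loses more. Bias scales with SD: at 5.5 the one-arm case is 0.5 × 5.5 × 0.350 = 0.96. The loss rates and correlations are assumptions; the article gives none by arm.

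**4. Power if all randomised patients are analysed.** Assume 30 per arm, SD 4.84, two-sided 0.05, a 4-point effect in those who reach four sessions and none in the rest. The average effect is 4 × (1 − f).

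| Falling short of four sessions | Average effect | Power |
|---|---|---|
| 0% | 4.0 | 88% |
| 10% | 3.6 | 81% |
| 20% | 3.2 | 71% |
| 25% | 3.0 | 66% |

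**The case against.** The strongest reply is that {20c} covers two subjects, non-adherence and missing data, and that each sentence answers one of them. Two analyses would then be intended: a completer analysis, and an intention-to-treat analysis with last observation carried forward. The article is also a condensed account, and the details of analysis sets may be in the full protocol or the SAP.

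Part of this stands. A reader might infer that no all-randomised analysis is planned at all. The text does not support that, because intention-to-treat analyses are named. But the two-analysis reading does not rescue the passage. The article does not say that two are meant, does not define the second set, does not say which is primary, and still gives the title of analysis population to the selected set. This is a stated numeric rule, not a detail left for later.

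A reader might also infer that the bias will favour CBT-I as the more demanding therapy. The article gives no basis for that. Session structure, frequency and duration are matched across arms, and the stopping and non-compliance rules apply to both. Control patients whose insomnia persists may also leave, which would shrink or reverse the bias. Nor is an error rate of about 9% a property of this plan; it belongs to one assumed scenario.

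**Conclusion.** The passage is wrong as written. Its one defined population conditions on a post-randomisation event, it is incompatible with the intention-to-treat analyses named alongside it, and no analysis is identified as primary. That conclusion depends on no calculation.

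The consequence is loss of protection by randomisation, not a bias of known size or sign. The illustrative range, from zero to about 0.8 ISI points either way, is at most about a fifth of the planned 4-point difference at an SD of about 4.84. Because the article does not allow anyone to say in advance where in that range the trial will fall, the all-randomised set should be primary.

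**What to change.** Replace the first sentence of {20c} with wording such as: The primary analysis includes all randomised patients in the arm to which they were allocated, whatever the number of sessions attended. Completion of at least four sessions defines a per-protocol set, used only for a labelled sensitivity analysis.

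Reconcile {11b} with this. As worded, patients leave the study, not only the therapy, for missed sessions, a medication change or an admission. Many with fewer than four sessions would then have no 12-week ISI, and the all-randomised analysis would rest on carried-forward values, often baseline. State that stopping or being withdrawn from the intervention does not end collection of the 12- and 24-week ISI. This concerns data collection only and leaves open when therapy should stop.

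The costs are a wording amendment, the effort of following patients who have stopped therapy, and an effect that may be smaller than in completers. On the assumptions above, power with 30 per arm would be about 71% if 20% fall short of four sessions and gain nothing, so the sample-size section should take this into account. The trial status section reports 5 of the planned 60 patients included by 12 January 2026, so the change can still be made early in recruitment.

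### For a missing week-12 ISI, LOCF can only carry baseline forward: the change is set to zero, which costs power under similar dropout and biases the comparison under unequal dropout

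*Protocol article*

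**What the plan says.** Under Outcomes {12}: "The primary outcome is improvement of the individual ISI score after 12 weeks". The same section fixes the schedule: "All outcomes are measured at baseline, after 12 weeks, and at 24 weeks, except for PSG", and PSG is taken only at baseline and week 12. No ISI is scheduled between baseline and week 12.

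The section on non-adherence and missing data {20c} has two sentences. The first reads "Included in the analysis population will be patients who have completed four therapy sessions". The second reads "We will use the Last Observation Carried Forward (LOCF)-principle as an imputation method for handling missing data for intention-to-treat (ITT) analyses". How the four-session population relates to the ITT analyses is not stated.

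Under Sample size {14}, at 80% power and alpha 0.05: "for detecting a between-groups effect of CBT-I on ISI of 4, follow-up data on 24 patients in each group is needed". The section adds that "an attrition rate of around 25% is expected" and sets the total at 60. The abstract's Methods paragraph says that both groups are expected to improve on the central outcomes, with CBT-I improving more on sleep.

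**The concern.** LOCF is often thought of as carrying a late, partly treated value to the endpoint. Here no such value exists for the primary outcome. A patient without a week-12 ISI receives the baseline score again, and so an improvement of exactly zero. The same holds for every missing week-12 PSG measure. The sleep diary in the CBT-I arm is not ISI and supplies nothing to carry. A patient who misses week 12 but attends week 24 is also scored as unchanged at week 12, because LOCF looks only backwards.

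At the attrition the protocol itself expects, about a quarter of the primary outcomes in an all-randomised analysis would be such zeros. If dropout is similar in the arms, the treatment difference shrinks and power falls. If dropout differs, the arm that loses more patients looks worse, even when the two therapies work equally well.

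**Working it through.** **Inputs from the protocol.** Difference 4 ISI points; 24 per group with follow-up data; power 80%; alpha 0.05 (taken as two-sided); 60 patients randomised 1:1, so 30 per arm; attrition about 25%.

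**Assumptions.** The SD, the control-arm improvement and the baseline-to-week-12 correlation (rho) are not given. I take rho as 0.3 to 0.5, changes of -3 in control and -7 in CBT-I, loss unrelated to outcome, and all 60 patients analysed.

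**1. The plan's own figure.** Solving n = 24, difference 4, power 80% for the SD gives 4.84 (t-test) or 4.95 (normal approximation). I use 4.85. With 25% loss, 60 × 0.75 = 45 patients remain (22.5 per arm). Observed-data power at SD 4.84 is then about 77% before any imputation. This small shortfall is separate from LOCF.

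**2. Effect under equal loss m.** LOCF effect = difference × (1 - m) = 4 × 0.75 = 3.0.

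**3. Power, change score.** The baseline-to-week-12 contrast in a repeated measures ANOVA is a comparison of change scores.
- SD of change = 4.85 × √(2(1 - rho)), which is 5.74 at rho 0.3 and 4.85 at rho 0.5.
- Under LOCF the variance in an arm is (1 - m) × SD² + m(1 - m) × (mean change)².
- At rho 0.3: CBT-I 0.75 × 32.93 + 0.1875 × 49 = 33.9; control 0.75 × 32.93 + 0.1875 × 9 = 26.4; pooled SD 5.49.
- At rho 0.5 the same steps give a pooled SD of 4.80.

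**4. Like-for-like power.** The LOCF columns have 30 per arm; the observed columns have about 22.5 per arm. The change-score figures follow from step 3, and simulation gives the same values. The ANCOVA figures are simulated, good to about one point.

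| rho | Change score, LOCF | Change score, observed | ANCOVA, LOCF | ANCOVA, observed |
|---|---|---|---|---|
| 0.3 | 55% | 63% | 65% | 80% |
| 0.5 | 66% | 77% | 72% | 86% |

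The cost of LOCF within a model is 63 - 55 = 8 and 77 - 66 = 11 points for change scores, and 80 - 65 = 15 and 86 - 72 = 14 points for ANCOVA.

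**5. Sensitivity to control improvement.** With a change-score SD of 4.84 and 25% loss, LOCF power is 74%, 70%, 63% or 55% if control improves by 0, 2, 4 or 6 points, against 77% for observed data. The cost therefore runs from 3 to 22 points.

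**6. Unequal loss.** LOCF effect = CBT-I improvement × (1 - CBT-I loss) - control improvement × (1 - control loss). With a common improvement c and no true difference, this reduces to c × (control loss - CBT-I loss).
- c = 5, loss 15% versus 35%: 5 × 0.20 = 1.0 spurious point against the arm with more loss; false positives about 11-15%.
- c = 5, loss 20% versus 30%: 5 × 0.10 = 0.5 point; false positives about 7%.
- Equal 25% loss, no true difference: about 5%, as nominal.
- True effect 4 (8 versus 4 points), CBT-I losing 35% and control 15%: 8 × 0.65 - 4 × 0.85 = 1.8. With the losses reversed: 8 × 0.85 - 4 × 0.65 = 4.2.

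**The case against.** Several points on the other side stand.

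- **The stated power is not voided.** A reader might infer this from the comparison of LOCF change scores (55-66%) with baseline-adjusted observed data (80-86%). That comparison changes the imputation and the covariate adjustment together. The sample size statement also refers to observed follow-up data. At rho 0.3, observed change scores reach only 63%, so most of the shortfall from 80% there is not due to LOCF.
- **The standard-error argument is not borne out here.** Single imputation is often criticised for understating uncertainty. With equal loss and no true effect, the LOCF test rejects at about 5%. The excess false positives come from unequal loss.
- **LOCF does not always shrink the effect, nor is it always conservative.** Shrinkage is certain only with similar dropout. Greater loss in the control arm offsets it, and in the last example above the estimate rises to 4.2.
- **Scope.** LOCF is tied to ITT analyses, while the sentence before it restricts the analysis population to patients with four sessions. If that restricted set carries the primary test, early dropouts leave it and fewer values are imputed. Those that are imputed still become baseline.
- **The unequal splits are illustrative.** The protocol gives no attrition by arm and matches the format of the two therapies. Its Discussion does acknowledge a risk of psychotic worsening from sleep restriction, which only CBT-I uses, so some imbalance is possible.
- **Zero change may be near the truth for some patients.** Those who leave after a few sessions with long-standing insomnia may have changed little. The alternative, missing at random, is equally untestable, and for a patient with neither follow-up ISI the data hold little beyond baseline.

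That a separate analysis plan may exist does not remove the point, because the protocol already fixes LOCF as the rule.

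**Conclusion.** The point holds. As written, LOCF for a missing week-12 ISI or PSG is baseline carried forward, an assumption of exactly no change that sits badly with the protocol's own expectation of improvement in both arms.

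At the expected 25% loss in each arm, a 4-point difference becomes 3.0. With the analysis model held fixed, power falls by about 8 to 15 points. These figures rest on the implied SD, the assumed changes of -3 and -7, dropouts who would have responded like completers, and all randomised patients being analysed. Other control improvements widen the change-score cost to about 3 to 22 points. Under unequal loss the direction of the bias depends on which arm loses more, and its size on a dropout gap that nobody can know in advance.

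For week 24 the point is weaker, because a week-12 value may be available to carry.

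**What to change.** In the section on missing data {20c}, replace LOCF with a likelihood-based mixed model for repeated measures. It should use all observed ISI values of all randomised patients, not only those completing four sessions, with terms for arm, visit, arm-by-visit and baseline ISI. The week-12 arm contrast is the primary estimate. Treat the continuous secondary outcomes in the same way.

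Add one sensitivity analysis under missing not at random, by delta-adjusted or reference-based multiple imputation. A reader who thinks dropouts gained little can then see what that belief does to the result.

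The cost is amended wording and modest programming. The Trial status section reports 5 patients included by January 2026, so the change can be made before most outcome data exist. The downside is that the main analysis assumes missing at random, which the sensitivity analysis probes but cannot test. No model recovers ISI values that are never collected.
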